### Timeline of the study

Participant recruitment was completed on 30 September 2024. Data collection is expected to be finalized by the end of November 2025, with results anticipated in January 2026.

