### Outcomes

A central element is the primary endpoint at the patient level (micro-level), which is divided into a three-tiered endpoint and allows conclusions about the benefits of the intervention. Tier 1 includes the frequency of access to the new form of care; Tiers 2 and 3 encompass the development and implementation of therapy proposals. The quantitative evaluation is supplemented by a quantitative patient survey using validated questionnaire instruments and a health economic assessment. In addition to quantitative data collection, interviews with patients are conducted to capture patient understanding of and expectations regarding personalized medicine. Overall, the development and enhancement of structures and processes in centers for personalized medicine (ZPM) is documented through standardized self-report questionnaires (see Appendix 2), as well as interviews and focus groups. This also specifically captures the exchange and knowledge transfer between ZPMs, as well as the extent to which an exchange of harmonized data has taken place. A complete list of the measures used in the quantitative and qualitative process evaluation, as well as secondary patient-related endpoints (clinical: response, PFS, OS, toxicity, patient questionnaires, and health economic measures), is presented in Table 2. A design diagram further elaborating on the data collection time points can be found in Appendix 3.

**Table 2 T2:** Primary and secondary endpoints and data collection.

Level	Evaluation	Primary endpoint	Time point	Instrument
Micro-level	Quantitative evaluation	Change in patient management based on the decision of the tumor board (assessed on three tiers):		Based on a quantitative questionnaire filled out by staff on site *(included in the provider questionnaire)*
		Tier 1: number of patients admitted to the tumor board	T0 = day of initial presentation at the tumor board)	
		Tier 2: proportion of patients with changed diagnostic strategy and/or therapy recommendation due to the decisions of the tumor board	T1 = day of therapy decision	
		Tier 3: proportion of patients with an actually implemented changed diagnostic strategy and/or therapy	T2 = day of the first therapeutic intervention	
		Secondary endpoints		
Micro-level	Quantitative evaluation	Clinical data of patients treated in the MTB • Response • Progression-free survival • Overall survival • Toxicities	event-driven	*Included in the provider questionnaire*

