### Participant timeline

Table 3 shows the participant schedule throughout the intervention period.

**Table 3 T3:** Participant schedule.

Specification of data collected	Participant schedule			
	Enrolment	2–3 months post-enrolment	5–6 months post-enrolment	Close-out
Time point/assessment	T0	T1	T2	T3
Study participation				
Eligibility screen	X			
Informed consent	X			
Allocation	X			
Clinical data collection				
Socio demographics	X			
Diagnose	X	X	X	
(Further) therapies in the last 3 months outside the MTB recommendation	X	X	X	
MTB recommendations		X	X	
Follow-up on MTB recommendations		X	X	
Scheduled end (follow-up completed after 5–6 months)				X
Reason for premature end				X
Patient questionnaire				
Socio demographics	X	X	X	
Living situation	X	X	X	
Financial Situation	X	X	X	
Social support	X	X	X	
EQ-5D-5L (health-related quality of life)	X	X	X	
EORTC QLQ-C30 (disease-related quality of life)	X	X	X	
FIMA (Utilization of health services)	X	X	X	
Patient satisfaction	X	X	X	
Patient interviews				
Understanding, expectations, and attitudes toward PM, perceived care		X	X	

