### Data collection and management

#### Quantitative evaluation

The primary endpoint contains three tiers. At Tier 1, the primary endpoint is the number of patients who receive an indication-driven, standardized access to the new form of care—personalized diagnostics and therapy—defined as access to the MTB. For this endpoint, a standardized data collection instrument will be developed to document both the original procedure and the newly implemented one, including the extent of the changes made (e.g., additional molecular diagnostics and therapy). The new procedure will be based on predefined, evidence-based criteria established by the ZPM network in BW. At Tier 2, it will be assessed for which patients the diagnostic process or diagnostic interpretation was significantly changed. Among this group, Tier 3 evaluates the proportion of patients for whom the changes ultimately led to treatment within the framework of personalized medicine. These changes may also include recommendations for genetic counseling, which—although not directly involving therapy or additional diagnostics—represent a modification in patient care.

Secondary clinical endpoints will be assessed continuously during the study: Adverse events (AEs) and serious adverse events (SAEs) will be recorded as they occur, and overall survival (OS) and progression-free survival (PFS) will be recorded every 6 months (T4–T8) until the end of the observation period, with a minimum follow-up of 6 months and an average follow-up of 12 months.

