##### Quantitative share of the process evaluation

Organizational structure and process survey: The qualitative analysis will be supplemented by a self-report questionnaire in accordance with the certification requirements of the German Cancer Society (Deutsche Krebsgesellschaft) (8). To assess the level of establishment of the individual ZPMs, the achievement of goals during the implementation of functional areas and their integration into the ZPM will be measured. This includes an established telemedicine access for external practitioners, quality-assured molecular diagnostics, and evidence-based therapy recommendations in interdisciplinary molecular tumor boards (MTBs).

In addition, a range of patient-reported outcomes (PROs) will be assessed. These include generic quality of life, measured using the standardized EQ-5D-5L questionnaire, and disease-specific quality of life, assessed with the EORTC QLQ-C30. An additional secondary PRO is treatment-related patient satisfaction, evaluated using the Patient Satisfaction with Cancer-related Care questionnaire (PSCC-G), which has been validated in German (13). All PROs will be collected at three individual time points: at the start of therapy (T2, baseline for secondary endpoints), after 3 months (T3), and after 6 months (T4).

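### The participant schedule ends clinical follow-up at 5–6 months, but the text promises 6-monthly OS and PFS recording with an average follow-up of 12 months

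*Protocol article*

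**What the plan says.** Four places in the protocol article bear on how long, and from when, OS and PFS are followed.

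- **Data collection and management, Quantitative evaluation.** The paragraph opens "Secondary clinical endpoints will be assessed continuously during the study". It then says "Adverse events (AEs) and serious adverse events (SAEs) will be recorded as they occur", and that "overall survival (OS) and progression-free survival (PFS) will be recorded every 6 months (T4–T8) until the end of the observation period". The same sentence ends by giving the length of follow-up: "with a minimum follow-up of 6 months and an average follow-up of 12 months".
- **Participant timeline, Table 3.** The columns are T0 (enrolment), T1 (2–3 months), T2 (5–6 months) and T3 (close-out). In the clinical data block, the T3 entry reads "Scheduled end (follow-up completed after 5–6 months". There is no T4 to T8.
- **Outcomes, Table 2.** Response, PFS, OS and toxicities are collected event-driven through the provider questionnaire. For the primary endpoint, "T2 = day of the first therapeutic intervention".
- **Quantitative share of the process evaluation.** Patient-reported outcomes are collected "at the start of therapy (T2, baseline for secondary endpoints), after 3 months (T3), and after 6 months (T4").

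Timeline of the study says that recruitment was completed on 30 September 2024 and that "Data collection is expected to be finalized by the end of November 2025". Analysis and anticipated results expects OS and PFS to improve among patients given targeted therapies, and says such outcomes would support the clinical value of the intervention.

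**The concern.** A centre cannot tell from these sections when to stop recording deaths and progressions. A centre that works from Table 3 closes each surviving patient at 5–6 months. A centre that works from the text continues at 6-monthly intervals to the end of observation. If all centres follow Table 3, OS and PFS are cut off at about 6 months and the stated average follow-up is out of reach. If centres differ, follow-up length varies by centre, and centre is tied to study arm here because the existing Baden-Württemberg centres contribute only intervention patients. In either case the expectation of better OS and PFS would rest on shorter or less even follow-up than the text describes.

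**Working it through.** **1. Stated follow-up against Table 3.** Inputs: minimum 6 and average 12 months (text); follow-up completed after 5–6 months (Table 3). If every patient's follow-up is at most 6 months, the mean is at most 6 months, which is half of the stated 12. The 6-month minimum is met only by patients closed at exactly 6 months. The stated figures cannot be reproduced from Table 3.

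**2. Stated follow-up against the calendar.** From 30 September 2024 to 30 November 2025 is 14.0 months. That is the potential follow-up of the last patient enrolled, so it is the smallest in the study; earlier patients have more. Follow-up well beyond 6 months is therefore feasible. A minimum of 6 with a mean of 12 is also coherent in itself: with uniform accrual over 12 months (assumed) and a cut-off 6 months after the last patient, the mean is 6 + 12/2 = 12 months. The conflict is with Table 3, not with the study period.

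**3. Where T4 to T8 fall.** The patient-reported outcome text puts T4 at 6 months after start of therapy. At 6-month spacing, T4 to T8 are then 6, 12, 18, 24 and 30 months. T5 to T8 all lie after Table 3's close-out. So does T4 for a patient whose therapy starts more than a few weeks after enrolment, because Table 3 counts from enrolment.

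**4. Labels side by side.**

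| Label | Table 2 (patient level) | Table 3 | Patient-reported outcomes text | Health economic analysis text |
|---|---|---|---|---|
| T0 | first presentation at the tumor board | enrolment | – | – |
| T2 | first therapeutic intervention | 5–6 months after enrolment | start of therapy | start of therapy |
| T3 | – | close-out | 3 months | 6 weeks |
| T4 | – | – | 6 months | 6 months |

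T2 is therefore either a baseline or the last scheduled assessment, depending on the section.

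**5. Size of the loss for OS.** The article gives no OS median, so these are assumptions: exponential survival from enrolment, with median m of 9, 12 or 18 months. The proportion dead by time t is 1 − 2^(−t/m).

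| Median (months) | Dead by 5.5 months | Dead by 12 months | Share of 12-month deaths missed |
|---|---|---|---|
| 9 | 34.5% | 60.3% | 1 − 34.5/60.3 = 43% |
| 12 | 27.2% | 50.0% | 1 − 27.2/50.0 = 46% |
| 18 | 19.1% | 37.0% | 1 − 19.1/37.0 = 48% |

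Closing at 5 months raises the missed share to 47%–53%; closing at 6 months lowers it to 39%–44%. About half is a fair summary.

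**6. What a 6-month PFS grid does.** Assume that only 6-monthly visit dates were kept and exponential PFS times were rounded up to the next visit. Medians of 3 and 4 months then both read 6, 6 and 8 read 6 and 12, and 8 and 10 both read 12. The hazard ratio is still recovered by a grouped-time or interval-censored analysis: 0.75 true and 0.75 from the grid; 0.80 and 0.80. The grid makes naive medians coarse, but PFS stays estimable.

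**The case against.** The best defence is that Table 3 lists only scheduled participant contacts, that the text governs OS and PFS, and that Appendix 3, which is not shown, elaborates the time points. Part of this stands. The absence of survival or toxicity rows from Table 3 is weak evidence on its own, since an article condenses. But the close-out line sits in the clinical data block, apart from the patient questionnaire block, and says that follow-up is completed. That is a printed statement against a printed statement.

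Several stronger readings are tempting and are not supported:

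- *All four clinical endpoints have conflicting rules.* They do not. For toxicity, event-driven collection and recording as events occur agree. Response has one timing rule. Only OS and PFS conflict.
- *Event-driven and 6-monthly recording are incompatible.* They can coexist if true event dates are entered at each 6-monthly update, which is the natural reading after "Secondary clinical endpoints will be assessed continuously during the study". No section says that event dates are rounded to visits.
- *OS and PFS could not be derived at all.* The article states no median, rate or hazard ratio for them. Both could be estimated up to 6 months even under Table 3, and step 6 covers a grid.
- *Detection delay differs by arm.* The intervention standardises imaging and response documentation, but no section gives arm-specific recording intervals or says that documentation dates replace event dates.
- *The calendar contradicts the 6 and 12 months.* The observation cut-off may precede the end of data collection, and deaths shorten average follow-up.

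The defence is also right that these are secondary endpoints whose p-values are not to be read confirmatively, and that the sample size does not depend on them.

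**Conclusion.** The contradiction is established from the text alone: Table 3 ends follow-up at 5–6 months, and the Quantitative evaluation text requires OS and PFS recording beyond that, with a 12-month average. Under Table 3 the mean is at most 6 months; this needs no assumption. The loss of about half of the deaths expected by 12 months (39% to 53% across close-out at 5 to 6 months) rests on assumed exponential survival with medians of 9 to 18 months. The inconsistent T-labels add to the problem, because neither the time origin nor the first OS/PFS time point can be fixed from them. This is a moderate correction: it concerns the length and origin of follow-up for two secondary, non-confirmatory endpoints and leaves the primary endpoint's definition and sample size untouched.

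**What to change.** Reconcile Outcomes (Table 2), Participant timeline (Table 3), Data collection and management (Quantitative evaluation) and the patient-reported outcomes text under Quantitative share of the process evaluation:

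1. State in Table 3 that the 5–6 month close-out does not end OS and PFS follow-up, and add the later OS/PFS recording to the table.
2. For every patient in both arms, record the actual date of death or last known alive and the actual date of first documented progression, up to one common data cut-off no later than the end of November 2025.
3. Name one time origin for OS and PFS, and give each T-label one meaning throughout, including the health economic text.
4. Where progression is known only to lie between two dates, analyse PFS as interval-censored.
5. Restate minimum and average follow-up for the chosen cut-off. With a cut-off at the end of November 2025, the last-enrolled patient has about 14 months of potential follow-up, and earlier patients more.

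The cost is wording plus one status extraction at database close. Recruitment is complete and the data collection period already covers it. The downside is some extra abstraction for patients treated outside the centre.

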#### Process evaluation

##### Qualitative share of the process evaluation

Semi-structured patient interviews: At the patient level, individual interviews with patients will complement the quantitative data collection. These interviews will focus not only on the qualitative assessment of processes from the patient's perspective but also on understanding their attitudes and perceptions toward patient management (PM). A total of 10–15 interviews with patients from various locations will be conducted, using a stratified selection based on age, gender, center, and condition throughout the entire intervention phase.

Semi-structured provider interviews: To identify possible obstacles and facilitating factors in the implementation process, qualitative surveys will be conducted in the form of individual interviews (*N* = 21) and focus groups (*N* = 3–4) with persons holding central roles (ranging from administrative, coordinative roles to medical roles) in the cancer centers toward the end of the implementation phase. The aim is to include staff from all participating centers in the interviews.

##### Quantitative share of the process evaluation

Organizational structure and process survey: The qualitative analysis will be supplemented by a self-report questionnaire in accordance with the certification requirements of the German Cancer Society (Deutsche Krebsgesellschaft) (8). To assess the level of establishment of the individual ZPMs, the achievement of goals during the implementation of functional areas and their integration into the ZPM will be measured. This includes an established telemedicine access for external practitioners, quality-assured molecular diagnostics, and evidence-based therapy recommendations in interdisciplinary molecular tumor boards (MTBs).

In addition, a range of patient-reported outcomes (PROs) will be assessed. These include generic quality of life, measured using the standardized EQ-5D-5L questionnaire, and disease-specific quality of life, assessed with the EORTC QLQ-C30. An additional secondary PRO is treatment-related patient satisfaction, evaluated using the Patient Satisfaction with Cancer-related Care questionnaire (PSCC-G), which has been validated in German (13). All PROs will be collected at three individual time points: at the start of therapy (T2, baseline for secondary endpoints), after 3 months (T3), and after 6 months (T4).

#### Health economic evaluation

For the purpose of the health economic evaluation, health-related quality of life, mortality, and cost data have to be collected for intervention and control patients. Quality of life is assessed based on patients' responses to the validated EQ-5D-5L questionnaire at study enrollment, 2–3 months after enrollment, and 5–6 months after enrolment (14, 15). Deaths are recorded in the questionnaire filled out by site staff. Inpatient treatment costs incurred at the university hospitals are extracted from the respective controlling departments. If the cancer treatment of patients does not take place at the study center itself, costs are approximated by the type of therapy recorded in the study documentation and the respective averages based on the then available controlling data from other patients. To capture other healthcare costs incurred outside the included university hospitals, an adjusted version of the FIMA questionnaire (questionnaire on the use of medical and non-medical health and care services in later life), a validated survey instrument for healthcare utilization for the German context (16, 17), is administered to patients at study enrollment, 2–3 months after enrollment, and 5–6 months after enrollment. Costs of the DNPM intervention itself are approximated through assessments made by coordinators of the study centers (a) in a quantitative survey (as part of the process evaluation questionnaire) and (b) in a focus group with the cost items of the DNPM project's overall budget as a starting point.

## Analysis and anticipated results

### Quantitative evaluation

The hierarchically organized endpoints described above (see Table 2) will be analyzed as binary variables (yes/no) while accounting for cluster effects from the individual centers using generalized estimating equations (GEE) in a logistic regression model (working correlation structure: exchangeable). The study arm (traditional procedure vs. standardized procedure according to the new form of care) will be coded as a binary variable, changing over time for centers newly included in the intervention condition. The Type I error rate will be set at 0.05 (two-sided). *P*-values for the secondary endpoints will be reported, but these should not be interpreted confirmatively. No corrections for multiple testing are necessary. Cluster effects will be addressed using GEE. In the primary analysis, we will use the independence estimation equation, and in a secondary analysis, we will use the exchangeable correlation structure within centers which allows for estimation of the cluster effect.

We expect the intervention to have a measurable impact on patient management as reflected in the primary outcome. Specifically, we anticipate the following effects across three levels of outcome assessment: Level 1, an increase in the frequency of indication-driven, standardized access to the MTB following implementation of the intervention; Level 2, a higher proportion of cases in which the recommendation for further diagnosis or therapy is modified as a result of MTB discussions under the harmonized approach; Level 3, an increase in the proportion of patients for whom the recommended changes in diagnostics or therapy are actually implemented in clinical practice. These analyses (Levels 1–3) will be additionally done with respect to the evidence level of the recommended therapies.

These expected changes reflect the underlying hypothesis that harmonization and standardization of personalized oncology care will enhance the integration of MTBs into clinical workflows and improve outcomes for patients. However, we have to take into account that harmonization is a complex process and implementation is not done on a certain date. Thus, in secondary analyses, we will exclude patients in the last 3 and 5 months before certification from the control group, and in an additional secondary analysis, we will analyze the time trend in centers that were newly certified, correcting for the time trend in centers that had been certified already at the beginning of the project. AEs and SAEs are expected to remain within acceptable limits, indicating good tolerability. Additionally, we expect improvements in OS and PFS, among patients receiving targeted therapies based on molecular tumor profiling. These outcomes would support the clinical value of the intervention in routine care.

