### Interventions

#### Explanation for the choice of comparators

The comparator consists of centers that have not yet completed the certification process to reflect the state of care prior to certification and to show the improvement in process-related and medical outcomes once the DNPM standard is established in the respective cancer center. Control patients at the sites meet the criteria for inclusion in the MTB but are not certified according to the standards of the DNPM in the MTB. The DNPM standard includes quality-assured molecular diagnostics as well as evidence-based treatment recommendations in interdisciplinary MTBs. Therapies initiated at the sites may vary individually by timing, duration, and type.

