### Strategies to improve adherence to interventions

Regular meetings will be held with study staff from all participating centers to improve data collection and documentation. Feedback from the centers will also be used to improve the design of the database and its interface. Besides this, all steps of the data collection will be regularly outlined at steering committee meetings, where all centers are present to ensure that centers understand the purpose of questionnaires, interviews, focus groups, etc. Next to this, updates on case numbers will be given regularly in these meetings to ensure that centers meet their recruitment goals. Additionally, questionnaires will be piloted with study staff in order to ensure that these are relevant to their daily work and are well understood.

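### As defined, Tier 1 of the primary endpoint is met by every enrolled patient in both arms, so the planned yes/no logistic GEE cannot estimate an arm effect for it

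*Protocol article*

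**What the plan says.** Four parts of the protocol article bear on this.

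- **Definition.** Table 2 (Outcomes) gives "Tier 1: number of patients admitted to the tumor board", with the time point "T0 = day of initial presentation at the tumor board". Under Data collection and management, Quantitative evaluation, Tier 1 is again a number of patients, namely those with standardized access on indication, "defined as access to the MTB". The Abstract also lists a number for Tier 1 and proportions for Tiers 2 and 3.
- **Who is enrolled.** The inclusion criteria (Eligibility criteria) require that the patient qualifies for the centre's MTB and is presented there for the first time. The section on the choice of comparators adds: "Control patients at the sites meet the criteria for inclusion in the MTB".
- **Analysis.** Under Analysis and anticipated results, Quantitative evaluation: "The hierarchically organized endpoints described above (see Table 2) will be analyzed as binary variables (yes/no". The method is "using generalized estimating equations (GEE) in a logistic regression model", with study arm coded as binary. At Level 1 the section expects "an increase in the frequency of indication-driven, standardized access to the MTB following implementation of the intervention".
- **Arm totals.** Sample size plans 3,507 intervention and 1,300 control patients. Existing centres supply intervention patients only, and new centres spend an assumed average of 6 months in the control phase. Recruitment describes active support of the centres, and the section on adherence strategies says that "updates on case numbers will be given regularly in these meetings to ensure that centers meet their recruitment goals".

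**The concern.** A logistic model can estimate an arm effect only if the outcome takes both values among the patients analysed and is not fixed by arm. Tier 1 coincides with a condition of entry. No patient outside the MTB enters the data set, so the data contain no one to whom access was refused or never offered.

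The first objective listed for the primary analysis, more patients with standardized access, rests on this tier. Software may still return a coefficient and a p-value for a degenerate outcome, and these could be reported as a result.

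**Working it through.** **1. The plan's own figure.** Sample size states 86% power for a 5-point difference with a two-sided 5% chi-squared test, ignoring clustering. No baseline proportion is given, so I centre it on 50% as an assumption: p1 = 0.475, p2 = 0.525, n1 = 1,300, n2 = 3,507.

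- Pooled proportion: (1,300 × 0.475 + 3,507 × 0.525) / 4,807 = 0.5115
- 1/n1 + 1/n2 = 0.001054
- SE under the null: √(0.5115 × 0.4885 × 0.001054) = 0.01623
- SE under the alternative: √(0.475 × 0.525 × 0.001054) = 0.01622 (both variances are 0.2494)
- Power: Φ[(0.05 − 1.96 × 0.01623) / 0.01622] = Φ(1.12) = 86.9%, or 86.2% with continuity correction

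The figure reproduces. The article does not say that this power refers to Tier 1.

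**2. Tier 1 as MTB access.** Every participant qualifies for and is presented at the MTB, so p1 = p2 = 1.

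- Data: 1,300/1,300 against 3,507/3,507
- Difference = 0; pooled p(1 − p) = 1 × 0 = 0; SE = 0
- Test statistic = 0/0, undefined
- Odds ratio = (3,507/0) / (1,300/0), undefined

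A binomial GEE with independence working correlation, fitted to 4,807 simulated records with a constant outcome, gave a perfect-separation warning, an arm coefficient of about 0 and p = 1. No sample size changes this.

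**3. Tier 1 as access to certified care.** Controls are by definition treated before certification and intervention patients after it.

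- Data: 0/1,300 against 3,507/3,507
- Odds ratio = (3,507 × 1,300) / (0 × 0), not finite

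The same GEE gave the warning and an unidentified coefficient of about 61. The result is the arm label. In steps 2 and 3 the fits only illustrate what the definitions imply. The argument rests on the definitions.

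**4. Raw totals as a substitute.** Sample size bases the 1,300 controls on seven new centres with 6 control months each, that is 7 × 6 = 42 centre-months, or 1,300 / 42 = 31.0 patients per centre-month. At exactly that rate, 3,507 intervention patients need 3,507 × 42 / 1,300 = 113 centre-months. The planned ratio of 3,507 / 1,300 = 2.70 can therefore arise with no change in access, purely from 113 against 42 centre-months. Recruitment support and case-number feedback act on the same totals.

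**The case against.** The strongest counter-argument is that Tier 1 may be a per-patient score. The data collection section speaks of access that is standardized and driven by indication, and plans an instrument recording the old and the new procedure against predefined criteria. The article also expects variation within the control condition and says that implementation does not happen on a single date. A yes/no for whether a patient's access met such criteria could vary in both arms, and the logistic GEE would then work. This stands as a possibility, so it would be too strong to say that no reading gives an estimable effect. But the article states no such criterion, and both Table 2 and the data collection section reduce Tier 1 to admission or access to the MTB.

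A second argument is that the binary sentence is loose condensation, with a count analysis left to an analysis plan that is not shown. The article does elsewhere treat Tier 1 as a number or frequency. Yet the sentence covers the Table 2 endpoints without exception, and the same section carries its expectations and further analyses through Levels 1 to 3. This is a stated rule that does not fit the endpoint, not an omitted detail.

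A third is that some consented patients may never reach the board. Presentation is itself an inclusion criterion, and any remaining *no* would measure loss between consent and board, not access to care.

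A reader might also infer that a failed Tier 1 test blocks Tiers 2 and 3, because the endpoints are called hierarchical. The article does not describe fixed-sequence testing, so that does not follow.

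**Conclusion.** The point holds for Tier 1 as defined: 100% against 100% if it means MTB access, or 0% against 100% if it means certified care. In neither case is there an estimable arm effect. The conclusion assumes that the inclusion criteria are applied as written and that no per-patient criterion for standardized access exists outside the article.

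It does not extend to the whole primary endpoint. Tiers 2 and 3 can differ between patients, and this defect leaves them testable. What is lost is a valid test for one of three primary tiers and for the first stated objective. The specification should be corrected before the analysis.

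**What to change.** Take Tier 1 out of the binary logistic analysis, report it descriptively by centre and period, and rest the confirmatory claim on Tiers 2 and 3. This changes wording only and needs no new data. The downside is that Tier 1 may become descriptive only.

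A formal analysis is possible if aggregate counts of first MTB presentations per centre and month, before and after certification, can be obtained. That is an assumption, since the article describes no such data. Recruitment closed on 30 September 2024, so the counts would have to be collected retrospectively. They could be analysed as a rate in a Poisson or negative binomial GEE clustered by centre, with study arm, an offset for months and a calendar-time term.

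If a per-patient criterion for standardized access was intended, it should be written down before the analysis, with a scoring rule that applies equally to control patients. Only then could Tier 1 stay in the logistic model.
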